### 2.16 Data management and monitoring

The case report form (CRF) includes observation time points, outcome measures, adverse events, and safety evaluations. The outcome assessors will be required to follow the requirements of the CRF and fill in the relevant information in a timely and accurate manner. Both paper documents and electronic records will be retained for at least 5 years after publication. In case of inquiries, readers are encouraged to reach out to the corresponding author for access to the original data. Protection of patient confidentiality is of paramount importance, encompassing details such as name, ID number, and telephone number. The research protocol will undergo scrutiny and refinement by experts in acupuncture, emergency procedures, methodology, and statistics. Adhering to a predetermined standard operating procedure, our approach incorporates patient screening, enhancement of relevant inspections, acupuncture administration, completion of CRFs, outcome assessments, and meticulous data management. Outcome assessments, CRF completion, and data management are maintained under rigorous supervision. The electronic data will be stored in the ResMan Research Manager repository. Anonymized trial data will be shared with other researchers at least 3 years after the article is published. If reviewers or readers have any questions regarding our published data, they can contact the corresponding author for access to the original data or visit ResMan (http://www.medresman.org/uc/project/projectadd.aspx). The Institutional Ethics Committee (IEC) at the Third Affiliated Hospital of Henan University of Chinese Medicine will oversee our activities independently of investigators and sponsors, conducting audits of trial conduct on a 12-month basis. Any alterations or corrections to operational procedures will be comprehensively documented through a breach report form, subject to monitoring, and submitted to the directors of the ethics committee and the China Clinical Trial Registration.

### 2.17 Data analysis

Data analysis will include case distribution, comparability analysis, efficacy analysis, analysis of factors affecting efficacy, and safety analysis. Statistical analyses will be conducted using PASS 18.0 statistical analysis software. First, a baseline analysis of the demographic characteristics of the cases in both groups will be conducted to assess the balance and comparability between the two groups. Subsequently, the efficacy and safety indicators of the two groups will be compared. For intra-group comparisons of quantitative data between the experimental and control groups, paired *t*-tests (or Wilcoxon signed-rank tests) will be used. Intergroup comparisons will use independent sample *t*-tests (or Mann–Whitney *U*-tests), and intragroup comparisons before and after treatment will use paired *t*-tests (or Wilcoxon paired signed-rank sum tests). Data obtained by performing repeated measurements at multiple time points will be analyzed using repeated measures ANOVA. Count data will be represented by proportions and rates, with intergroup comparisons of overall efficacy using chi-squared tests (or Fisher's exact test). Intergroup comparisons of proportions will use a 2 × C table chi-squared test. The generalized estimating equation (GEE) model will be used to assess how the primary outcome measures, HAMA, change over time across the two intervention groups. Covariates, such as demographic factors and other relevant variables, will be included in the model to account for potential confounding effects. The GEE model will also be used to examine the effects of the intervention on secondary outcome measures. The GEE model will estimate the average change in outcome measures over time within each intervention group and compare the differences in changes between the intervention and control groups. Interaction terms may be included in the model to examine whether the effects of the intervention vary over time or across different groups of participants. All statistical tests will be two-sided, with a significance level of α =0.05. A *p*-value of < 0.05 will be considered to indicate statistical significance. To better quantify actual changes, missing values will not be inputted. All significance tests will use pairwise missing values, with an alpha value of 0.05.

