## 2 Methods/design

### 2.1 Study setting

This study will be a parallel randomized controlled clinical trial with the participants blinded to their groups. The research will be conducted in accordance with the principles outlined in the Consolidated Standards of Reporting Trials (CONSORT) and the Standards for Reporting Interventions in Clinical Trials of Acupuncture (STRICTA). A total of 56 participants diagnosed with GAD comorbid with naturally occurring PSD (i.e., nighttime sleep duration ≤ 6 h) will be recruited, and 28 healthy volunteers will also be recruited as a control group. Participants will be randomly assigned at a 1:1 ratio to either the acupuncture group or the sham acupuncture group. The establishment of the sham acupuncture group is intended to provide clearer evidence of the therapeutic effects of acupuncture and to compare these effects with the placebo effect of sham acupuncture. Both the acupuncture and sham acupuncture interventions will be conducted over a 2-week period, with sessions conducted three times a week. The study will be conducted at the Third Affiliated Hospital of Henan University of Chinese Medicine in Henan Province, China. The research will follow the Standard Protocol Items: Recommendations for Interventional Trials (SPIRIT) guidelines (32). For the participant timeline, see Figure 1.

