### 2.15 Sample size

According to the results of a pilot study (58), after 8 weeks of treatment, the HAMA scores were 9.00 ± 3.2 in the treatment group and 10.83 ± 3.06 in the control group. Sample size estimation using a two-tailed test for a study with a paired design for two-sample mean comparison, a significance level of α = 0.05 (two-tailed), and a power of 1–β = 0.90 was performed. Using PASS 15.0 to estimate the difference between the two groups' HAMA as 0.915, assuming a common standard deviation of 1.83, the sample size was estimated using a two-sample test assuming equal variances in PASS 15.0. The estimation formula (60) is:

$$\begin{array}{l} n=\frac{2\times {\left(u_{\alpha }\;+\;u_{\beta }\right)}^{2}\sigma^{2}}{\delta } \end{array}$$

Considering ~20% potential dropout during the observation period, the calculated sample size was calculated to be ~28 cases per group, and the total number of participants was determined to be 56.

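### Section 2.17 promises a group-by-time contrast for HAMA, makes interaction terms optional in the next sentence, and does not commit to baseline HAMA as a covariate

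*Protocol article*

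**What the plan says.** Three statements in Section 2.17 bear on the HAMA model.

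- The contrast: "The GEE model will estimate the average change in outcome measures over time within each intervention group and compare the differences in changes" between the two arms. This is a firm commitment.
- The terms: the following sentence reads "Interaction terms may be included in the model to examine whether the effects of the intervention vary over time", and goes on to mention differing effects across groups of participants. This is optional.
- The covariates: "Covariates, such as demographic factors and other relevant variables, will be included in the model to account for potential confounding effects". Baseline HAMA is not mentioned either way.

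The same section lists independent-sample t-tests (or Mann-Whitney tests) between arms, with no adjustment. It states no variance estimator, working correlation or reference distribution for the GEE. The abstract places evaluations at weeks 0, 1 and 2. Section 2.14 adds a follow-up two weeks after treatment ends, without saying in the text which scales are repeated then.

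**The concern.** When the baseline score is one of the repeated outcomes, the treatment effect sits in the group-by-time term. The group main effect alone averages in the baseline visit, where randomisation makes the expected difference zero. The plan promises the right contrast but groups the term that carries it with exploratory interactions. An analyst could follow the second sentence, fit group and time only, and report a diluted effect.

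The covariate rule gives the wrong reason for adjusting. Between randomised arms the main gain is precision, and the baseline value of the outcome is usually the strongest candidate. Here it is collected from every participant, yet the plan does not commit to it. A difference in change uses the baseline score, but less efficiently than conditioning on it. In a trial of this size that loss of precision matters.

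**Working it through.** **Inputs**

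- Two-sided testing: "All statistical tests will be two-sided, with a significance level of α =0.05" (Section 2.17).
- Design target: "a significance level of α = 0.05 (two-tailed), and a power of 1–β = 0.90 was performed" (Section 2.15).
- Effect and SD used for sizing: "estimate the difference between the two groups' HAMA as 0.915, assuming a common standard deviation of 1.83" (Section 2.15), a standardised effect of 0.915/1.83 = 0.5.
- Arms: 28 per group at 1:1. With about 20% dropout, 28 × 0.8 = 22.4, so about 22 completers per arm.
- Correlation ρ of HAMA between visits: not given. Assumed 0.3 to 0.8, with equal variance at each visit.

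**1. The plan's own sample size**

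n = 2(1.960 + 1.282)²/d² per group, then divide by 0.8.

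- d = 0.5 (the stated inputs): 84.06, rounded up to 85; 85/0.8 = 106.25, so 107 per group. The stated 28 is not reproduced.
- d = 1.0 (1.83/1.83): 21.01, rounded up to 22; 22/0.8 = 27.5, so 28 per group. This matches.

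The sample size is a separate matter. It is relevant here only because, at the stated effect and SD, the trial has little precision to spare.

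**2. Group coefficient when group-by-time is omitted**

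With complete data and equal weight per visit, the coefficient is the mean of the visit-specific effects, including zero at baseline.

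| Visits (weeks) | Pattern of effect | Share recovered | Of 0.915 points |
|---|---|---|---|
| 0, 1, 2 | full from week 1 | (0+1+1)/3 = 67% | 0.61 |
| 0, 1, 2 | half at week 1 | (0+0.5+1)/3 = 50% | 0.46 |
| 0, 1, 2, 4 | full from week 1 | (0+1+1+1)/4 = 75% | 0.69 |
| 0, 1, 2, 4 | half at week 1, then held | (0+0.5+1+1)/4 = 63% | 0.57 |

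**3. Variance of the between-arm contrast at one visit**

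In units of σ², the factor is 1 for an unadjusted post-treatment score, 2(1−ρ) for a change score and 1−ρ² for a baseline-adjusted score. Adjusted over change is therefore (1+ρ)/2.

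| ρ | Saving against change, 1−(1+ρ)/2 | Saving against unadjusted post score, ρ² |
|---|---|---|
| 0.3 | 35% | 9% |
| 0.5 | 25% | 25% |
| 0.7 | 15% | 49% |
| 0.8 | 10% | 64% |

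**4. Power at standardised effect 0.5**

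Noncentral t, two-sided α = 0.05, 2n−2 degrees of freedom, noncentrality d*·√(n/2). Here d* = 0.5/√(2(1−ρ)) for change and 0.5/√(1−ρ²) for baseline-adjusted. The one degree of freedom spent on the covariate is ignored.

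| ρ | 22 per arm: change → adjusted | 28 per arm: change → adjusted |
|---|---|---|
| 0.3 | 27.8% → 39.7% | 34.2% → 48.7% |
| 0.5 | 36.7% → 46.5% | 45.1% → 56.4% |
| 0.7 | 55.2% → 62.1% | 66.0% → 73.0% |
| 0.8 | 72.6% → 77.0% | 82.8% → 86.5% |

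**The case against.** The best defence is that the plan does commit to the contrast. The sentence on differences in changes is firm, and the optional sentence can be read as covering extra terms: effects that differ between visits, or subgroup effects. This largely stands. A reader might infer that the plan has no treatment contrast, and the document does not support that. Dilution arises only if the analyst sets the first sentence aside. What remains is a conflict between adjacent sentences over a term that the primary comparison needs.

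On covariates, a reader might infer that baseline HAMA is left out of the model. That also goes too far, because the open-ended wording leaves room for it. A difference in change is valid under randomisation, so this is a matter of efficiency and not bias, and the gain shrinks as ρ rises. But permission is not commitment, and conditioning on baseline is at least as efficient across the assumed range.

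A reader might also infer that the GEE inflates type I error with so few participants. The article names no type of standard error, and that detail is commonly left to an analysis plan. Even if uncorrected sandwich errors with a normal reference were assumed, a single contrast without covariates would have a type I error of about 6.0% (28 per arm) to 6.2% (22 per arm). Nor does anything in the document make GEE the wrong method; choosing a mixed model instead would be a preference.

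**Conclusion.** The point holds in two parts. First, Section 2.17 contradicts itself on whether the group-by-time contrast is a fixed part of the HAMA model. If the optional reading were followed, the group coefficient would recover about 50-67% of the effect, or 63-75% with a week-4 HAMA. These shares assume complete data, equal visit weights and the effect patterns shown.

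Second, the section does not commit to baseline HAMA as a covariate. Relative to a difference in change, this forgoes a variance saving of 35% to 10% for ρ from 0.3 to 0.8. At standardised effect 0.5 the power forgone runs from about 12 points (ρ = 0.3) to 4 points (ρ = 0.8) with 22 per arm. The figures rest on an assumed ρ and equal variances; the direction is the same throughout the range.

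No conclusion about inflated type I error follows from the document.

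**What to change.** In Section 2.17:

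1. State that the HAMA model always contains group, visit and group-by-visit, and that the primary comparison is the between-arm contrast at one named visit.
2. Keep the optional wording for subgroup interactions only.
3. Use post-baseline HAMA as the outcome and name baseline HAMA as a covariate. Give precision as the reason, and list any other covariates in advance.
4. Use the same form for each secondary scale, with its own baseline.

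GEE can stay. As advice only, the analysis plan could name a small-sample correction for its standard errors. The cost is a few sentences and the model code; no new data are needed.

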### 2.5 Dropout criteria

Included subjects will be dropped from the study in the following cases:

1) Subjects with poor compliance who quit on their own during the treatment.2) Those who use treatment methods prohibited by this plan or change the treatment method on their own.3) Cases where serious adverse reactions or complications occur and are not suitable for continued treatment and the trial is terminated.

Dropped cases will be handled as follows:

1) After the subject drops out, the attending doctor will try to contact the subject to ask for the reason by visiting them after making an appointment by phone or letter, and they will then record the last treatment time and complete the assessable items.2) For cases that quit the trial due to adverse reactions or ineffective treatment, the attending doctor will take appropriate measures according to the actual situation of the subjects.3) The “Summary of Treatment Completion” and “Clinical Trial Completion” in the CRF will be filled in.4) All excluded and dropped cases will be subjected to intention-to-treat analysis after the trial ends.

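### Intention-to-treat analysis is promised for all dropped cases, but the fixed no-imputation, pairwise-deletion rule turns the week-2 HAMA tests into available-case comparisons

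*Protocol article*

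**What the plan says.** Section 2.5 (Dropout criteria) ends its handling rules with "All excluded and dropped cases will be subjected to intention-to-treat analysis after the trial ends". The same section lists grounds on which participants are dropped, among them "Those who use treatment methods prohibited by this plan or change the treatment method on their own", and it gives instructions "For cases that quit the trial due to adverse reactions or ineffective treatment". After dropout the attending doctor is to contact the participant, ask for the reason, and "record the last treatment time and complete the assessable items". Nothing is said about keeping to the planned HAMA visits.

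Section 2.15 (Sample size) expects appreciable loss: "Considering ~20% potential dropout during the observation period, the calculated sample size was calculated to be ~28 cases per group".

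Section 2.17 (Data analysis) states "To better quantify actual changes, missing values will not be inputted. All significance tests will use pairwise missing values". It lists independent-sample t-tests or Mann-Whitney tests for between-group comparisons, repeated-measures ANOVA for data at several time points, and a GEE model for HAMA over time. It does not say which of these decides the primary outcome. No working correlation or weighting is given for the GEE.

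**The concern.** A participant who leaves before week 2 without a week-2 HAMA value cannot enter a week-2 between-group test when nothing is imputed and missing values are deleted. A standard repeated-measures ANOVA drops that participant altogether. A report could therefore carry the intention-to-treat label on tests that leave out about one randomised participant in five.

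This matters because leaving for lack of effect, for adverse reactions or to take other treatment is plausibly related to anxiety scores. If such leaving differs between acupuncture and sham, the participants still observed are no longer comparable by randomisation. HAMA is the primary outcome, and section 2.12 makes the value of the secondary results depend on its significance. The rule is written for all significance tests, so a later analysis plan would have to overturn it, not merely add detail.

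**Working it through.** **1. Participants affected.** Section 2.15 gives 28 per group, 56 in total, with about 20% dropout.
- Absent at the end: 56 × 0.20 = 11.2, about 11.
- Observed per group: 28 × 0.80 = 22.4.

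The figure of 28 serves here only as the number randomised. It does not follow from the stated difference of 0.915 and SD of 1.83, which is a separate matter on which this point does not depend.

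**2. What each planned analysis does with a participant lost after week 1.**
- t-test or Mann-Whitney on week-2 HAMA: participant absent (available case).
- Repeated-measures ANOVA: participant absent at all visits (complete case).
- GEE: baseline and week-1 values kept.

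**3. Bias of the raw week-2 contrast.** Let p be the dropout share in an arm and g the mean HAMA of missing minus observed participants. The observed arm mean lies p × g below the full mean. The sham-minus-acupuncture difference is therefore understated by

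pS × gS − pA × gA.

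Two SDs are used: 1.83 (section 2.15), and the pooled SD of the cited 8-week HAMA results, √((3.2² + 3.06²)/2) = 3.13. The values of g are assumptions.
- 20% in each arm, g equal: 0.2g − 0.2g = 0.
- 20% in each arm, sham dropouts 1 SD worse, acupuncture dropouts no different: 0.2 × 1.83 = 0.37 to 0.2 × 3.13 = 0.63 points.
- 30% sham and 10% acupuncture, all dropouts 1 SD worse: (0.3 − 0.1) × SD, again 0.37 to 0.63 points.
- 20% in each arm, only acupuncture dropouts 1 SD worse: the same size with the opposite sign, so the effect is overstated.

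The planned difference is 0.915 points.

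**4. Simulation.** True effect 0.915/1.83 = 0.50 SD at week 2; visits at weeks 0, 1 and 2; normal data with exchangeable correlation 0.5 or 0.7; 400,000 per arm. Score-driven dropout is logistic on the week-1 score with slope 1 per SD. Apart from the effect and the visit times, these inputs are assumptions.

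| Dropout pattern | Raw week-2 contrast, correlation 0.5 / 0.7 |
|---|---|
| 20% per arm, score-driven in both | 0.50 / 0.50 |
| 20% per arm, score-driven in sham only | 0.41 / 0.38 |
| 30% sham score-driven, 10% acupuncture random | 0.37-0.38 / 0.32 |
| 30% sham, 10% acupuncture, score-driven in both | 0.42 / 0.39 |
| 20% per arm, score-driven in acupuncture only | 0.58-0.59 / 0.62 |

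Relative to 0.50, the understatement runs from 0.08/0.50 = 16% to 0.18/0.50 = 36%. The overstatement reaches 0.12/0.50 = 24%.

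On the same data, GEE with an exchangeable working correlation gave about 0.50 in every row. GEE with an independence working correlation gave the same figures as the raw contrast. A completers' change from baseline also gave about 0.50. That result relies on baseline and week 2 being equally correlated with week 1, which holds here by construction.

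**5. Type I error of the week-2 t-test at 28 per arm.** Correlations between visits were 0.5-0.7, and dropout was driven by the week-1 or week-2 score.
- Dropout alike in both arms: about 5%.
- 20% per arm, score-driven in one arm only (slope 1.5): 8-13%.
- 10% against 30% with the same mechanism (slope 1): 6.5-8.4%.

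**The case against.** The best defence is that section 2.17 plans a GEE model for HAMA over time, and GEE keeps the observed visits of those who drop out. In the simulation it was unbiased with a correct working correlation, so the bias in the table belongs to the raw week-2 contrast and not to every planned analysis. The working correlation is a detail that may properly sit in an analysis plan not shown. This stands as a limit on the size of the problem. It does not remove it: the same section prescribes t-tests and ANOVA alongside GEE without ranking them, applies pairwise deletion to all tests, and leaves open an independence structure that gives no protection.

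Four stronger readings are tempting and are not supported.
- A reader might infer that no imputation and intention-to-treat can never coexist. They can, when a suitable longitudinal model uses every observed visit of everyone randomised. The conflict is with the named endpoint tests and the pairwise rule.
- A reader might take the 20% as outcome-related. Section 2.15 gives an all-cause allowance, and section 2.5 names outcome-related reasons without frequencies.
- A reader might infer that the HAMA result will be biased. If share and mechanism are alike in both arms the bias is zero. Participant blinding with a same-point, same-device sham and a two-week course make similar dropout plausible.
- A reader might infer that dropouts are not assessed at all. Section 2.5 asks the doctor to complete whatever can be assessed at dropout. It does not promise the planned visits, but it does not rule them out.

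**Conclusion.** The point holds in this limited form. The intention-to-treat promise in section 2.5 is not what the t-test, Mann-Whitney test or repeated-measures ANOVA in section 2.17 deliver under a fixed no-imputation, pairwise rule, and about 11 of 56 participants may be affected. This is a stated rule that can give a wrong answer, not a detail left for later.

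The contradiction is certain; the bias is a risk. For the raw week-2 contrast, a true 0.50 SD could appear as about 0.32-0.42 SD or about 0.58-0.62 SD, depending on which arm loses its worse participants. Those ranges rest on assumed differences in dropout between arms and assumed correlations. They do not apply to a GEE with a well-chosen working correlation, which the plan neither requires nor designates as primary.

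**What to change.** Reconcile sections 2.5 and 2.17.

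- **Section 2.17:** replace the blanket no-imputation and pairwise rule with one primary longitudinal HAMA analysis. It should include all randomised participants as allocated, use every observed visit, and be valid under missing at random. A likelihood-based mixed model for repeated measures would serve, as would GEE with a suitable non-independence working correlation or weighting. The choice between them is secondary to naming one. Add one sensitivity analysis that departs from missing at random, for example delta-adjusted multiple imputation, because dropout may depend on the unobserved week-2 score.
- **Section 2.5:** state that stopping study treatment or using other treatment does not by itself end HAMA assessment at the planned visits for participants who still consent. This concerns data collection only and leaves clinical management as it is. It should be in force before participants drop out, since ratings not taken cannot be recovered.

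Cost: a few sentences of revised text, slightly more analysis work, and a few extra HAMA ratings. The sample size and visit schedule do not change.
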